### Follow-up

Primary and secondary outcomes will be measured using the instruments described at baseline and 0, 4, 8 and 13 weeks. Follow-up assessments will be performed using a telephone call at 2 weeks after the first treatment and self-completed postal questionnaires at all other time points. Non responders will be telephoned 1 week after mailing the follow-up questionnaire on up to 2 occasions and posted a replacement questionnaire with a reminder letter if there is still no response at 2 weeks.

### Criteria and procedure for withdrawal of patients from the trial

A patient may be withdrawn or themselves withdraw from the trial at any time, at his/her own discretion or at that of the GP or researcher if there is any suspicion of adverse effects or an exclusion condition (including loss of capacity to consent) supervening. The reasons for interrupting the patient's participation in the trial will be recorded on the summary page of the Data Record Book (DRB) and the patient ' proforma. His/her GP will be notified of the need for clinical follow up.

### Justification of sample size

Assuming an intracluster correlation coefficient (ICC) of 0.01 we need at least 15 practices per arm and a cluster size of 20 (i.e. 20 patients in each practice) giving 300 patients per arm to detect a difference of 1 point in the PSQI with 90% power for a definitive RCT. This would require a major investment of resources and therefore we will first conduct an exploratory trial to understand the feasibility of a full trial. For our exploratory trial we will take a pragmatic decision to include 4 practices, 2 intervention and 2 control practices.

### Methods of data collection

Patient level data will be collected from patients using self-report questionnaires, and researchers by telephone. Outcomes will be measured at baseline and at week 0, at 4 weeks, and at 8 and 13 weeks from the initial treatment whether treatment has been completed or not (i.e. on an intention to treat basis).

### Data analysis

Data collection and statistical analysis will be undertaken on both clustered data and on individual patient data masked to treatment allocation and on an intention to treat basis. Data will be analysed at baseline, at 0, 4, 8 and 13 weeks. Baseline clinical and demographic data will be analysed for important differences between trial groups. Comparisons between treatment arms before and after intervention will be made using proportions and odds ratios. We shall analyse the primary outcome using linear regression with baseline as a covariate and also controlling for other relevant baseline covariates. We shall analyse our primary outcome, the PSQI, at the level of the patient using a multivariable model which adjusts for baseline PSQI and for the clustering due to practices. We shall carry out similar analyses for our secondary outcomes. In addition we shall extend our model to incorporate all the time points. This will be a mixed effects model with random effects for time and practice. This model has the advantage that sporadic missing data can be coped with if it is missing at random (MAR). If there is substantial dropout we shall examine it using a pattern mixture model which does not have the restriction to MAR. We shall conduct analogous analyses for the other secondary outcomes. Statistical significance will be set at 5% (two tailed) and analysis performed using Stata or other statistical software. No interim analysis of the primary or secondary outcomes will be undertaken during the trial period.

Template analysis will be used to undertake a qualitative analysis of a short telephone interview (20 minutes) to investigate perceptions of practitioners and patients on interventions delivered and received in each practice with 4 patients and 4 practitioners from each intervention and control practice.

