## Abstract

**Background:**

Sleep problems are common, affecting over a third of adults in the United Kingdom and leading to reduced productivity and impaired health-related quality of life. Many of those whose lives are affected seek medical help from primary care. Drug treatment is ineffective long term. Psychological methods for managing sleep problems, including cognitive behavioural therapy for insomnia (CBTi) have been shown to be effective and cost effective but have not been widely implemented or evaluated in a general practice setting where they are most likely to be needed and most appropriately delivered. This paper outlines the protocol for a pilot study designed to evaluate the effectiveness and cost-effectiveness of an educational intervention for general practitioners, primary care nurses and other members of the primary care team to deliver problem focused therapy to adult patients presenting with sleep problems due to lifestyle causes, pain or mild to moderate depression or anxiety.

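### A two-tailed 5% significance rule is set for outcome comparisons in a feasibility pilot with two practices per arm, and the text leaves open whether every analysis accounts for practice

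*Protocol article*

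**What the plan says.** All references are to the Protocol article.

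- **Test level.** Data analysis describes between-arm models for the primary and secondary outcomes and then states: "Statistical significance will be set at 5% (two tailed) and analysis performed using Stata or other statistical software". Nothing there marks these comparisons as exploratory.
- **Size.** Justification of sample size says a definitive trial needs at least 15 practices per arm with 20 patients each, "to detect a difference of 1 point in the PSQI with 90% power for a definitive RCT". For the pilot it makes a pragmatic choice to "include 4 practices, 2 intervention and 2 control practices". The Practices gives 80 patients in total.
- **Clustering.** Data analysis opens with "Data collection and statistical analysis will be undertaken on both clustered data and on individual patient data". It then says "Comparisons between treatment arms before and after intervention will be made using proportions and odds ratios", and mentions a linear regression with baseline covariates; neither sentence refers to practice. The next sentence gives a patient-level PSQI model that adjusts for baseline and for practice clustering. Similar analyses are planned for secondary outcomes, and the longitudinal mixed model has a practice random effect.
- **Purpose.** Aims and Study design say the pilot tests procedures and refines the sample size, and Aims assigns the effectiveness hypotheses to the main trial. The Abstract calls it "a pilot study designed to evaluate the effectiveness and cost-effectiveness of an educational intervention", and the Abstract's Discussion says it will determine whether outcomes improve. Health economic analysis opens by placing the cost-utility evaluation in the main study, but later says this study will estimate cost-effectiveness and produce an acceptability curve.

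**The concern.** A 5% rule invites each comparison to be read as significant or not significant. With two practices per arm, neither reading carries much information. A non-significant PSQI result is the expected outcome even if the definitive trial's target effect is real. A significant one may reflect a difference between practices if the analysis behind it ignores practice or relies on large-sample theory.

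The rule also does not fit the stated feasibility aim, and the Abstract and part of the economic section point readers towards an effectiveness conclusion. At stake is how the pilot's outcome results will be reported and understood by those planning the definitive trial.

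**Working it through.** **Inputs from the plan.** Two-sided alpha 0.05; ICC 0.01; 20 patients per practice; definitive trial 15 practices (300 patients) per arm, 90% power, 1 PSQI point; pilot 2 practices (40 patients) per arm. The PSQI SD is not stated.

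**1. Reproduce the definitive-trial figure and recover the SD.**
- Design effect = 1 + (20 − 1) × 0.01 = 1.19.
- Effective patients per arm = 300 / 1.19 = 252.1.
- From n = 2 × SD² × (1.960 + 1.282)² / 1², SD² = 252.1 / (2 × 10.51) = 12.0, so SD ≈ 3.46.
- Check: SD 3.46 needs 252 × 1.19 ≈ 300 per arm, or 15 practices. SD 3 would need 12 practices per arm and SD 4 would need 21. The stated figure is coherent, but it cannot be verified without the SD. I therefore use 3.46 as an assumption, with range 3 to 4.

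**2. Precision of the pilot.**
- SE of the difference = SD × √(2 × 1.19 / 40) = 3.46 × 0.2439 = 0.844.
- Between-practice degrees of freedom = 4 − 2 = 2, so the critical t is 4.303.
- The 95% half-width is 4.303 × 0.844 = 3.63 points. A normal-theory interval would show 1.96 × 0.844 = 1.65.
- Power comes from the noncentral t on 2 df. The detectable difference is 5.65 × SE for 80% power and 6.80 × SE for 90%.

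| SD | SE | 95% half-width | Power for 1 point | Detectable at 80% | Detectable at 90% |
|---|---|---|---|---|---|
| 3.00 | 0.732 | 3.1 | 13% | 4.1 | 5.0 |
| 3.46 | 0.844 | 3.6 | 11% | 4.8 | 5.7 |
| 4.00 | 0.976 | 4.2 | 10% | 5.5 | 6.6 |

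**3. Type I error at nominal 5%.** If practice is ignored, the approximate error is 2 × (1 − Φ(1.96 / √design effect)).
- ICC 0.01: 1.96 / √1.19 = 1.797, giving 7.2%.
- ICC 0.05 (an assumption; design effect 1.95): 1.96 / √1.95 = 1.404, giving 16.0%.

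A simulation of 200,000 null trials with 4 practices of 20 and no covariates gave:

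| Analysis | ICC 0.01 | ICC 0.05 |
|---|---|---|
| Practice ignored | 7.3% | 16.4% |
| Random intercept, REML, z test | 5.4% | 10.0% |
| Random intercept, ML, z test | 7.3% | 14.2% |
| Cluster-robust SE, t on 3 df | 12.0% | 12.1% |
| Practice-level t test, 2 df | 5.0% | 5.0% |

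The protocol names none of these reference distributions. The rows show how far the result depends on that choice.

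**The case against.** The strongest reply is that the plan does handle clustering. The multivariable PSQI model adjusts for practice, secondary outcomes follow it, the mixed model has a practice random effect, Study design commits to the cluster extension of CONSORT, and the economic section says cluster randomisation must be reflected. This stands. A reader might infer that the plan analyses patients as if practices did not exist, but no sentence says so. The phrase about individual patient data may mean patient-level modelling, and the linear-regression sentence may be a first description of the adjusted model. What remains is ambiguity about those sentences and the odds ratios.

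A reader might also infer that every p-value and interval will be invalid. That is not supported either. A 2-df test keeps 5% under normality, REML with a z test is near nominal at the plan's ICC, and neither z-based nor cluster-robust inference is specified. The choice of degrees of freedom is commonly left to an analysis plan, so its absence is not the fault here. With 6 possible allocations the smallest two-sided permutation p-value is 2/6 = 0.33, but no permutation test is planned, so this only illustrates how little 2 v 2 can show.

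On odds ratios, hypnotic use and adverse effects can be summarised as proportions; removing that sentence would be a preference. Baseline adjustment, which is planned, would lower the residual SD and narrow the interval, but it adds no practice-level degrees of freedom.

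On purpose, most of the document states the feasibility aim clearly, and the later economic text may be describing the main trial. Finally, no text ties progression to a significant PSQI result, so an effect on that decision is possible rather than shown.

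**Conclusion.** The point holds as a mismatch between rule, design and aim. The document fixes a two-tailed 5% rule, without an exploratory label, for a comparison in which the 95% interval is about ±3.6 PSQI points (3.1 to 4.2) and power for the definitive trial's 1-point target is about 11% (10% to 13%). These figures rest on the plan's ICC of 0.01, full recruitment of 20 patients per practice, no baseline adjustment, and an SD back-solved from the sample-size statement. A higher ICC would make them worse.

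It would go too far to say that no effect could be concluded. A very large one could be shown: about 4.8 points at 80% power (4.1 to 5.5 over the SD range). If any between-arm analysis ignored practice, its type I error would be about 7% at ICC 0.01, and 16% at ICC 0.05, a value the protocol does not give. Large-sample cluster methods can also exceed 5%. The effectiveness and cost-effectiveness wording in the Abstract and the later part of Health economic analysis conflicts with the feasibility aim stated elsewhere.

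**What to change.** 1. In Data analysis, drop the 5% significance rule for the pilot and label all outcome comparisons exploratory.
2. State that every between-arm model accounts for practice, including the linear regression, any analysis of individual patient data and any odds ratios for binary outcomes.
3. Report the PSQI difference with a 95% interval, either from practice-level summaries with t on 2 df or from the mixed model with small-sample degrees of freedom (Kenward-Roger or Satterthwaite).
4. Make the feasibility estimates (recruitment, retention, data completeness, fidelity) the main results.
5. Align the Abstract (Background and Discussion) and the later paragraphs of Health economic analysis with Aims, Study design and the opening of Health economic analysis.

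These are wording changes; design, recruitment and data collection stay as they are. The cost is a wider reported interval: about ±3.6 points instead of the ±1.65 that a normal-theory interval would show on the same assumptions.

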### Health economic analysis

Since a cost analysis will be undertaken for the main trial and the instruments and methods will be piloted in this study, the rationale and methods are therefore described below. Given the high cost of insomnia and the need for economic research in this area, the economic evaluation for the main study will estimate the cost-utility of a brief educational intervention for primary care teams (GPs, nurses and practice managers) to improve sleep management using problem focused therapy (including CBTi) compared to usual care provided by GPs and nurses from a health and social care perspective in the base case. The wider costs will be captured separately. Established and accepted economic methodologies will be employed throughout.[28,29]

Resource items likely to change as a result of the intervention (as well as the cost of developing and providing the educational intervention) will be identified, measured and valued drawing upon instruments used in other studies and available from published resources.[30] The base case will capture only those costs incurred by the NHS and social care (including, for instance, patient visits to health and social care professionals, outpatient visits and admissions to secondary care, and medication) using patient level data extracted from self completion questionnaires administered at baseline, 0, 8 and 13 weeks. This will include all health and social care resource use (due to the difficulties of disentangling) which are consumed as a result of sleep problems per se rather than because of other causes. Where feasible the wider costs associated with sleep problems will be monitored through patient questionnaires, in particular we will attempt to estimate patient costs, particularly associated with health care usage (for instance, over the counter medication and travel costs) and the productivity costs (both absenteeism and presenteeism) [31,32] of patients, whether due directly to sleep problems or accidents, to see if the intervention has any impact on the patient's wider well-being. Unit costs will be derived from national published data (for instance, NHS reference costs,.[33] Annual Survey of Hours and Earnings (ASHE)) for the most recent price year available or local unit costs will be estimated where appropriate and feasible.

This study will undertake cost-effectiveness and cost utility analyses. Both types of analyses enable technical efficiency questions to be addressed, that is to ask, is an educational intervention for health professionals a cost effective way in which to improve the management of patients with sleep problems? In addition, cost-utility analysis will also enable allocative efficiency questions to be addressed within the health sector, for instance, is the brief educational intervention about CBTi considered in this study cost-effective compared to a diverse range of other health interventions or services? This study will estimate the cost-effectiveness in terms of cost per 1 point change on the Pittsburgh Sleep Quality Index (PSQI) and the cost utility using the EuroQol EQ-5D [26] to estimate the cost per QALY over the trial period. Both outcome instruments will be administered at baseline and 13 weeks to observe if change occurs as a result of the intervention and whether it is sustained.

The timeframe for the economic analysis will be that of the trial period. The change in costs will be divided by the change in effectiveness in order to estimate the cost effectiveness of the brief educational intervention compared to no brief educational intervention for health professionals. If non-dominance occurs (that is if costs are greater and the intervention is more effective or if the intervention is cheaper and less effective) an incremental cost-effectiveness ratio (the ratio of change in cost divided by change in benefit) will be produced. The confidence region around the incremental cost effectiveness ratio will be estimated using appropriate statistical techniques. Since this economic evaluation is being undertaken alongside a cluster randomised trial the analysis needs to reflect the increased uncertainty of randomising clusters rather than individuals, a number of approaches have recently been proposed each found to generate similar findings.[34] The stochastic analysis will enable a cost effectiveness acceptability curve to be produced [35] illustrating the decision uncertainty, that is the probability that the brief educational intervention for health professionals on improving sleep management is cost-effective compared to no educational intervention/usual care for a range of willingness to pay per QALY values.

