### Outcomes

The ***primary outcome measure ***will be global sleep quality as measured by PSQI at baseline and at 0, 4, 8 and 13 weeks.

***Secondary outcomes ***will be measured at baseline and at 0,4,8 and 13 weeks and will include the effect of the intervention on sleep outcome measures assessed with PSQI and sleep diaries [23]: self reported Sleep Onset Latency (SOL, how long it takes to fall asleep), Wake time After Sleep Onset (WASO, total hours awake at night after one has fallen asleep), total Time In bed (TIB) and Sleep Efficiency (SE). Sleep Efficiency, expressed as a percentage, is calculated as follows: SE = (100-[(SOL + WASO/TIB) × 100]). Research has shown that these subjective measures of sleep reflect subjective treatment-related improvements.

We will also measure daytime sleepiness (Epworth sleepiness scale),[24] anxiety and depression using the Beck Depression Inventory,[25] health-related quality of life using EuroQol EQ-5D,[26] psychological outcome profile (PSYCHLOPS)[27] and frequency of use and mean dose of hypnotic medication. Patients will also keep a Data Record Book (DRB) to record any adverse effects that they might experience during the treatment period. Cost-effectiveness will be assessed using the methods below.

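### The economic section's two-point schedule for EQ-5D and PSQI conflicts with the five-point outcome schedule and could bias QALYs in either direction; its base-case cost rule contradicts itself

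*Protocol article*

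**What the plan says.** The Protocol article gives three sets of time points that bear on the economic evaluation.

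- **Outcome schedule.** The Outcomes section says the primary outcome "will be global sleep quality as measured by PSQI at baseline and at 0, 4, 8 and 13 weeks". It lists "health-related quality of life using EuroQol EQ-5D" with the secondary outcomes, which carry the same times. Follow-up repeats this: "Primary and secondary outcomes will be measured using the instruments described at baseline and 0, 4, 8 and 13 weeks". Methods of data collection agrees and counts the weeks from initial treatment.
- **Economic outcomes.** Health economic analysis names PSQI for cost-effectiveness and EQ-5D for cost-utility, the latter "to estimate the cost per QALY over the trial period". On timing it says: "Both outcome instruments will be administered at baseline and 13 weeks to observe if change occurs as a result of the intervention". That sentence closes by adding a second aim for the two readings: "and whether it is sustained".
- **Resource use.** The same section takes costs from "self completion questionnaires administered at baseline, 0, 8 and 13 weeks".

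On which costs count in the base case, the section says: "This will include all health and social care resource use (due to the difficulties of disentangling) which are consumed as a result of sleep problems". The sentence ends by excluding use that has other causes.

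Participant recruitment plans 3 months of recruitment under usual care. Randomisation and allocation concealment says allocation is identified once patient recruitment is complete. Treatment starts within 10 working days of allocation or, in intervention practices, after team training.

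**The concern.** The economic wording describes when the instruments are given, and its two times are not the five set elsewhere for the same instruments. It also fails its own purpose: one post-treatment reading cannot separate a change that lasted from one that had just appeared or had already begun to fade.

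QALYs depend on the path of EQ-5D between readings. With two readings, only a straight line between them is available. The cost per QALY and the acceptability curve use that quantity, so a wrong path moves both.

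The starting point matters too. Baseline is taken at enrolment and week 0 at the start of treatment. An early recruit's baseline can precede treatment by about 3 months. The economic sentence names baseline and leaves out week 0.

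The cost rule is a separate contradiction. Its stated reason, that causes are hard to separate, supports counting everything. Its closing restriction requires the separation that the reason says is difficult. The two readings give different numerators for the cost-effectiveness ratio.

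**Working it through.** **No plan figure to reproduce.** The article states no QALY value and no rule for computing QALYs. The check is therefore how far a two-point calculation could depart from one that uses the scheduled visits.

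**Inputs.** Visits at weeks 0, 4, 8 and 13, from Outcomes and Follow-up; horizon 13 weeks, so 13/52 = 0.25 year.

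**Assumptions.** The arms are equal in EQ-5D at baseline and week 0; a full between-arm difference of 0.05 (the percentages do not depend on it); the paths below; no discounting.

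**Formula.** Incremental QALY = sum over intervals of (interval length in weeks × mean of the differences at its two ends) / 52.

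**Step 1: weeks counted from treatment start.** For every path that ends at 0.05, the two-point value is 13 × 0.025 / 52 = 0.00625.

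| Assumed difference at weeks 0, 4, 8, 13 | Four-point QALY | Two-point QALY | Error |
|---|---|---|---|
| Linear: 0, 0.0154, 0.0308, 0.05 | 13 × 0.025 / 52 = 0.00625 | 0.00625 | 0% |
| Complete by week 4: 0, 0.05, 0.05, 0.05 | (4 × 0.025 + 9 × 0.05) / 52 = 0.01058 | 0.00625 | -41% |
| Complete by week 8: 0, 0.025, 0.05, 0.05 | (8 × 0.025 + 5 × 0.05) / 52 = 0.00865 | 0.00625 | -28% |
| Only after week 8: 0, 0, 0, 0.05 | (5 × 0.025) / 52 = 0.00240 | 0.00625 | +160% |
| Transient: 0, 0.05, 0.025, 0 | (4 × 0.025 + 4 × 0.0375 + 5 × 0.0125) / 52 = 0.00601 | 0 | -100% |

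**Step 2: line drawn from a baseline g weeks before week 0**, with no true difference during the gap. The two-point value becomes (13 + g) × 0.025 / 52. Against the linear path (0.00625):

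- g = 2: 15 × 0.025 / 52 = 0.00721, +15%
- g = 6: 19 × 0.025 / 52 = 0.00913, +46%
- g = 13: 26 × 0.025 / 52 = 0.0125, +100%

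The gap can reverse the direction seen in Step 1. At g = 13 the error is 0.0125 / 0.01058 = 1.18 (+18%) where the gain is complete by week 4, and 0.0125 / 0.00865 = 1.44 (+44%) where it is complete by week 8. The two errors cancel at g = 0.55 / 0.025 - 13 = 9 weeks and g = 0.45 / 0.025 - 13 = 5 weeks respectively. A transient gain still scores zero whatever the gap.

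**Step 3: the cost sentence.** No arithmetic applies. A visit for an unrelated condition is included under the first half and excluded under the second. An analyst or questionnaire designer cannot follow both.

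**The case against.** A reader might infer that EQ-5D and PSQI are collected only twice, that the interim data are discarded, and that the QALYs are wrong. The text does not support this. The word only does not appear, no QALY formula is given, and the outcome sections still schedule both instruments at weeks 0, 4 and 8. The section also commits itself to accepted economic methods, and an article may leave the formula to a fuller plan. Two points are exact under linear change. Nor may one infer that QALYs would be understated: the error can run either way, and the pre-treatment gap can turn an underestimate into an overestimate. These objections stand and limit the claim to a conflict and a risk.

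It can also be said that:

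- Resource-use forms that skip week 4 need not lose data, because a form can cover the whole interval since the last one. This stands; the different times alone are not shown to do harm.
- Cost per PSQI point needs only the change to the end point, so the QALY argument does not reach it. This stands; for PSQI the fault is the schedule conflict.
- The section also aims at resource items that the intervention is likely to change, which leans towards the narrower cost rule. So the choice is open, but it still has to be made.
- This is a four-practice pilot and no decision will rest on its cost-effectiveness ratio. This lowers the weight. It does not remove the point, because the section says the economic instruments and methods are being piloted here, and Study design lists data collection procedures among the things to be tested.

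**Conclusion.** Two contradictions hold on the text: the times at which EQ-5D and PSQI are given, and the scope of base-case costs. Neither is merely missing detail, since each pairs statements that cannot both be followed.

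The effect on QALYs is conditional. If the economic schedule governed, the error would range from -100% to +160% over the paths examined with weeks counted from treatment start, and would be nil for linear change. Where a difference remains at week 13, counting the gap before treatment moves the estimate upward. These sizes rest on assumed paths, equal arms at the start and assumed gaps; the article contains no data to choose among them. It is a correction worth making, of limited weight in a pilot. Its main value is that the definitive trial would otherwise inherit an unsettled schedule and cost rule, and EQ-5D forms not sent at weeks 4 and 8 cannot be recovered.

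**What to change.** In Health economic analysis:

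1. State that EQ-5D and PSQI are collected at baseline and weeks 0, 4, 8 and 13, as in Outcomes and Follow-up. Baseline must stay in the list.
2. State that QALYs are the area under the EQ-5D curve from week 0 to week 13, using the week 0, 4, 8 and 13 values, adjusted for EQ-5D at baseline. Week 0 should not be the adjusting value: by then allocation has been disclosed, intervention teams have been trained, and practices and patients are not masked. Baseline is taken before disclosure, and Data analysis already adjusts the primary outcome for its baseline value.
3. Count costs over the same week 0 to 13 window.
4. Keep one base-case cost rule. The reason the section gives supports all health and social care use, with sleep-attributed use as a sensitivity analysis.

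The cost is a few sentences and a few lines of analysis. No visits are added, because the forms are already scheduled. The downsides are that all-cause costs are more variable, that the sensitivity analysis needs the questionnaire to record which use is put down to sleep, and that a QALY built from four forms is more often incomplete than one built from two.
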